### Secondary endpoints

2.10

The secondary endpoints are as follows:

1.Technical success rate: Technical success is defined as the stent being placed between the duodenum and common bile duct at 1 day after treatment in the EUS-CDS group, and the stent being placed across the papilla and the biliary stricture on CT at 1 day after treatment in the ERCP group.2.Clinical success rate: Clinical success is defined as improvement in T-Bil to less than 1.3 mg/dL or improvement in T-Bil or alkaline phosphatase levels to <50% of the highest pretreatment values within 14 days after treatment.3.Procedure-related AE rate: Early AEs (within 14 days after treatment) are defined according to the Cotton criteria^[12]^ and the ASGE lexicon for endoscopic AEs,^[13]^ and include postprocedural pancreatitis, cholecystitis, non-occlusion cholangitis, stent migration, stent deviation, liver abscess, bleeding, intestinal perforation, and abdominal pain. Late AEs (>14 days until 180 days after treatment) are defined according to the ASGE lexicon for endoscopic AEs, and include nonocclusion cholangitis, stent migration, and stent deviation.4.Procedure time: Procedure time is defined as the time from the puncture of the bile duct to stent placement in the EUS-CDS group, and from the time of biliary cannulation to stent placement in the ERCP group.5.Re-intervention success rate: Re-intervention success is defined as the placement of a new drainage tube at the fistula in the EUS-CDS group, and the placement of a new transpapillary drainage tube in the ERCP group.6.Technical success rate in cases not requiring fistulous-tract dilation (only EUS-CDS group).7.Overall survival time.8.Rate of patients receiving post-drainage chemotherapy: The rate of post-drainage chemotherapy is defined as the percentage of patients who receive at least 2 courses of chemotherapy after drainage.

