### Inclusion criteria

2.4

The following inclusion criteria will be applied:

1.Age ≥ 20 years.2.Radiological diagnosis (with or without pathological confirmation) of malignancy and presence of a malignant distal biliary obstruction and dilation of the upstream bile duct that is unresectable or presents a very high surgical risk.3.Written consent obtained following adequate explanation of the study aims, design, and procedures.

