### Primary endpoint

2.9

The primary endpoint is the stent patency rate at 180 days after stent insertion. The stent patency rate is defined as the percentage of patients who do not experience stent dysfunction from the date of stent insertion to 180 days after treatment.

Stent dysfunction is defined as follows:

1.If the lowest serum total bilirubin (T-Bil) value in the blood tests performed after treatment is <1.5 mg/dL: a serum T-Bil level of ≥3.0 mg/dL and a bile duct diameter greater than that on the pretreatment imaging.2.If the lowest serum T-Bil value in the blood tests performed after treatment is more than 1.5 mg/dL: a serum T-Bil level >2.0 times the lowest value and a bile duct diameter greater than that on the pretreatment imaging.

Patients who are lost to follow-up or who die without stent dysfunction will be censored at the last observation date. Patients without technical success will be censored at the treatment date.

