### Definition of an AE

4.1

An AE is defined as any unfavorable or unintended illness or disability and its manifestations occurring in a subject up to 14 days after the end of the protocol treatment, regardless of whether it is causally related to the protocol treatment. A clinically significant worsening of symptoms that existed before the study is also considered an AE. However, worsening of the primary disease is not included as an AE. Physiological changes that are not considered clinically important in terms of frequency or severity will not be considered as AEs. If an AE is observed in a subject, then the principal investigator (or sub-investigator) will immediately ensure the safety of the subject, take appropriate measures, and describe the event in the case report.

In principle, CTCAE v5.0 should be used for the evaluation of adverse events/adverse reactions. However, for the following events, diagnosis, and severity assessment should be performed according to the respective criteria.

1.Postprocedural pancreatitis: Cotton criteria.^[12]^2.Cholecystitis, nonocclusion cholangitis, stent migration, stent deviation, liver abscess, bleeding, intestinal perforation, and abdominal pain: ASGE guidelines.^[13]^

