## Discussion

5

This multicenter single-blinded RCT study is designed to assess whether EUS-CDS with a novel stent shows superior stent patency to ERCP with a traditional metal stent when used for the first-line drainage of malignant distal biliary obstruction. This clinical trial will also compare the rates of technical success, clinical success, procedure-related AEs, re-intervention success, patients receiving post-drainage chemotherapy, and procedure and overall survival time.

Currently, the criterion standard procedure for malignant biliary drainage is transpapillary drainage with ERCP, whereas EUS-CDS is the modality of choice when ERCP fails in patients with distal bile duct obstruction. The major problem affecting transpapillary drainage with ERCP is stent dysfunction due to tumor tissue stent ingrowth and/or overgrowth.^[3,4]^ By contrast, stent tumor tissue ingrowth or overgrowth does not occur after EUS-CDS because the drainage route passes beside the tumor. Therefore, EUS-CDS is expected to have longer stent patency than ERCP. If stent patency rate is shown to be higher in EUS-CDS than in ERCP, it would be clinically significant because it would not only reduce the number of re-interventions, but could also affect oncologic outcomes. In patients with unresectable pancreatic cancer with a good performance status, there is a clear survival benefit attributable to FOLFIRINOX therapy^[14]^ and nab-paclitaxel plus gemcitabine therapy,^[15]^ which are delayed if re-interventions for biliary obstruction are needed.

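### Cholangitis from a blocked stent can be counted neither as a patency failure nor as a named procedure-related adverse event

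*Protocol article*

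**What the plan says.** Section 2.10, item 3, defines the procedure-related AE rate in two windows. Early events (to day 14) are defined by two published classifications "and include postprocedural pancreatitis, cholecystitis, non-occlusion cholangitis, stent migration, stent deviation, liver abscess, bleeding, intestinal perforation, and abdominal pain". Late events (after day 14, to day 180) are defined by one of these "and include nonocclusion cholangitis, stent migration, and stent deviation". Section 4.1 uses the same non-occlusion term when it names the events that have their own grading criteria.

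Section 2.9 defines stent dysfunction by two rules, according to the lowest bilirubin after treatment. With a nadir below 1.5 mg/dL, dysfunction is "a serum T-Bil level of ≥3.0 mg/dL and a bile duct diameter greater than that on the pretreatment imaging". With a higher nadir, it is "a serum T-Bil level >2.0 times the lowest value and a bile duct diameter greater than that on the pretreatment imaging". Both rules join a bilirubin condition to a duct condition. Neither mentions cholangitis, symptoms or re-intervention.

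Section 2.4 admits only patients with "presence of a malignant distal biliary obstruction and dilation of the upstream bile duct". The duct reference in section 2.9 is therefore a duct that was already dilated when it was imaged.

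**The concern.** The qualifier on cholangitis makes sense if the two endpoints fit together: non-occlusive cholangitis goes to safety and occlusive cholangitis goes to patency. They do not fit. Section 2.10 hands occlusive cholangitis over, and section 2.9 takes it only if bilirubin and duct width both pass their limits. Cases in between belong to neither endpoint.

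This matters because the abstract and section 6 make a change of first-line drainage depend on patency and safety together. Infection from a blocked stent bears on both. If it can fall outside both, each endpoint under-counts a stent complication, and sites that read the lists differently will count it differently.

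The shorter late list adds to this. Cholecystitis, liver abscess, bleeding and intestinal perforation are named to day 14 and not afterwards, although the stent stays in place and follow-up for this endpoint runs to day 180.

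**Working it through.** **Setting the definitions side by side.** The patients below are constructed for illustration.

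1. *Bilirubin condition missed.* Nadir 0.8 mg/dL; at day 70 cholangitis from a blocked stent, with bilirubin 2.4 mg/dL. The nadir is below 1.5, so the first rule applies. 2.4 is below 3.0, so this is not dysfunction under 2.9, whatever the duct width. The event is occlusive, so it is not on the late list of 2.10.

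2. *Duct condition missed.* Same nadir, bilirubin 5 mg/dL, duct wider than after drainage but no wider than before treatment. 5 exceeds 3.0, but the duct condition fails, so again this is not dysfunction and not a named AE. Section 2.11 schedules CT on days 1, 14 and 180 only, so at day 70 the duct condition depends on unscheduled imaging.

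3. *Early against late.* To day 14, section 4.1 records any unfavourable illness regardless of cause, so an early occlusive cholangitis is at least recorded as a general AE. After day 14 that definition no longer applies.

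4. *Serious events.* Section 4.2 covers events at any time after the procedure and lists hospital admission as a criterion, so an admitted patient may be reported there. But 4.2 defines a serious event as a kind of AE, and 4.1 limits AEs to 14 days, so even this is not certain. Reporting under 4.2 also does not enter the event in the AE rate of 2.10.

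5. *List lengths.* The early list names nine events and the late list three. The six that drop out are postprocedural pancreatitis, cholecystitis, liver abscess, bleeding, intestinal perforation and abdominal pain.

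**What the planning rates say about direction.** Inputs from section 3.1: 180-day patency 85.1% (EUS-CDS) and 48.9% (ERCP), exponential times, deaths 10% per month in both arms, 12 months of enrolment and 6 months of further observation.

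The plan's own figures first. Hazard ratio = ln(0.851)/ln(0.489) = 0.2255. Schoenfeld events at two-sided 0.01 and 90% power = 4 × (2.576 + 1.282)² / (ln 0.2255)² = 26.8, so 27, close to the stated 29. With death as a competing hazard, the mean event probability is (0.157 + 0.483)/2 = 0.320, and 29/0.320 = 90.6, against the stated 90. 90/0.95 = 94.7, so 95.

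Dysfunction before death by month 6 = λ/(λ+μ) × [1 − exp(−6(λ+μ))], with μ = −ln(0.9) = 0.1054 per month:

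- EUS-CDS: λ = −ln(0.851)/6 = 0.0269; 0.2033 × (1 − 0.4523) = 11.1%.
- ERCP: λ = −ln(0.489)/6 = 0.1192; 0.5309 × (1 − 0.2599) = 39.3%.

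The ratio is 39.3/11.1, about 3.5. If occlusions that escape section 2.9 arise in proportion to those it counts, more would escape in the ERCP arm. That proportionality is an assumption, so this supports a direction and not a size.

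**The case against.** The other side has several fair points.

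- **Keeping the two kinds of cholangitis apart is a legitimate design.** It keeps patency failures out of the safety rate and avoids counting one event twice. This stands as a reason for the flag. It does not excuse a case that neither endpoint takes.
- **The lists are not stated to be closed.** The wording is inclusive. This stands in part: a site could count occlusive cholangitis. But on an open reading the non-occlusion qualifier and the shorter late list have no function, and sites may differ.
- **Other reporting may catch the event.** Serious AE reporting may capture admitted patients, and a re-treated stent contributes to re-intervention success. This narrows the hole, most clearly to non-serious cases after day 14. Neither puts the event into the AE rate that describes each arm.

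Three stronger readings are tempting and are not supported.

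- **Disease worsening.** Section 4.1 states that "worsening of the primary disease is not included as an AE", and a reader might infer that a stent blocked by tumour could be excluded this way. Nothing in the protocol classes stent occlusion or its cholangitis as disease worsening. Sections 2.9 and 5 treat it as stent dysfunction. The gap follows from 2.9 and 2.10 without this clause.
- **An established bias favouring ERCP.** Section 5 says "The major problem affecting transpapillary drainage with ERCP is stent dysfunction due to tumor tissue stent ingrowth and/or overgrowth" and expects neither mechanism after EUS-CDS. A reader might infer that the loss falls almost wholly on ERCP. But no rate of occlusive cholangitis is given by arm, the ERCP stent is fully covered (section 2.8), and migration is listed for both arms. Section 3.2 plans AE percentages with 99% confidence intervals per group and no test between arms.
- **A percentage of patients missed.** One might take a share of the 39.3% and 11.1%. Those are planned dysfunction events, whereas missed events would be additional to whatever 2.9 counts, and any share would be invented. A power loss derived from such a share has the same weakness. Nor is the 5% AE rate quoted in the introduction a yardstick: it comes from a study of EUS-CDS with this stent and says nothing about ERCP.

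**Conclusion.** The gap is real and follows from the text alone. Occlusive cholangitis that fails either the bilirubin or the duct condition of section 2.9 is not a patency failure, and section 2.10 does not name it as a procedure-related AE. Followed as written, the plan under-counts a stent complication, most clearly after day 14 and in patients who are not admitted. The late list also leaves out several events that are named only to day 14.

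No magnitude can be given: the protocol states neither the share of occlusive cholangitis that misses a condition nor any rate by arm. A larger loss in the ERCP arm is plausible on the planning rates, provided that escaping events arise in proportion to counted ones. The protocol does not establish it. The point is worth correcting because the remedy is specific and cheap.

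**What to change.** - In 2.10 item 3 and in 4.1, replace non-occlusion cholangitis with cholangitis of any cause, in both the early and the late window, with a flag for occlusive or non-occlusive. Report the non-occlusive rate as a subset, so that the rate now planned is still available.
- Extend the late list to those early-list events that can occur late, at least cholecystitis, liver abscess, bleeding and perforation.
- Reconcile 2.9, 2.10 and 4.1 so that every stent-occlusion cholangitis is counted in at least one endpoint, and say which.

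The first change alone puts these events into the safety endpoint. It leaves section 2.9 as it is, so the constructed patients above would still count as patent. Whether they should is a question the reconciliation has to answer openly.

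The cost is protocol and case report form wording. Reported AE rates rise somewhat in both arms, and some events appear in both endpoints, where the flag identifies them.

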### EUS-CDS procedure

2.7

An echoendoscope is inserted orally and advanced to the duodenal bulb. Biliary accessibility is then confirmed via EUS from the duodenal bulb, with Doppler imaging used to rule out any intervening vessels. A 19-gauge fine aspiration needle is used to puncture the extrahepatic bile duct under endosonographic guidance. After the bile juice is aspirated, contrast medium is injected and a 0.025 inch guidewire is advanced into the common bile duct. Thereafter, an attempt is made to insert the novel stent (8 mm; Covered BileRush Advance, Piolax Medical Devices, Yokohama, Japan) via the fistula without using any dilation devices. If successful, the metal stent is expanded between the common bile duct and the duodenum under EUS guidance. If the delivery system cannot be advanced via the fistula, the fistulous tract is dilated using dilation devices. The stent diameter is 8 mm, and the stent length is determined at the discretion of the endoscopist.

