### ERCP procedure

2.8

ERCP-assisted transpapillary stenting is performed using a standard duodenoscope. Following biliary cannulation, contrast medium is injected to obtain a cholangiogram.

After confirmation of successful bile duct cannulation, biliary sphincterotomy is performed. Finally, a fully covered self-expandable metal stent (X-Suit NIR; Olympus Medical Systems, Tokyo, Japan) is placed across the papilla and the biliary stricture. The stent diameter is 10 mm, and the stent length is determined at the discretion of the endoscopist.

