### Statistical analysis

3.2

In the effectiveness analysis for the population, analysis of the full analysis set is the main analysis, and per protocol analysis is performed as a reference. The safety analysis for the target population will analyze all test examples. For the stent patency rate at 180 days after stent insertion, the *P* value for the difference between the two procedures will be calculated using a 2-sample log-rank test. The Kaplan–Meier method will be used to estimate survival curves for each group. Greenwood's formula will be used to estimate the confidence interval for the stent patency rate at 180 days after stent insertion, and Brookmeyer and Crowley's method will be used to estimate the confidence interval for the median rate. For the rates of technical success, clinical success, technical success in cases not requiring fistulous-tract dilation, procedure-related AEs, re-intervention success, and patients receiving post-drainage chemotherapy, the percentages, and 99% confidence intervals will be calculated for each group. For the procedure time, the mean and 99% confidence interval will be calculated for each group. For the overall survival time, the *P* value for the difference between the 2 groups will be calculated with a 2-sample log-rank test. A *P* value of ≤.01 will be considered statistically significant. All analyses will be performed using JMP Pro version 14 (SAS Institute, Inc., Cary, NC).

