## Conclusions

6

This study is designed to assess whether EUS-CDS with a novel stent is superior in terms of stent patency to ERCP when the procedures are used for first-line drainage of malignant distal biliary obstruction. If EUS-CDS is superior to ERCP for first-line drainage for malignant distal biliary obstruction in terms of stent patency and safety, it is expected that interruption to chemotherapy due to stent dysfunction and adverse effects will be avoided, and that EUS-CDS may replace ERCP as the first-line drainage method.

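### Two minor points on secondary endpoints: procedure time starts at different steps in the two arms, and the stated per-group intervals do not deliver the between-arm comparison that the Discussion promises

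*Protocol article*

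**What the plan says.** **Procedure time.** Section 2.10 of the protocol article defines it for one arm as "the time from the puncture of the bile duct to stent placement in the EUS-CDS group" and for the other as "from the time of biliary cannulation to stent placement in the ERCP group". It does not say whether the ERCP clock starts at the first cannulation attempt or at success.

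The procedure descriptions show how each step is used. In section 2.8, contrast follows cannulation, and then: "After confirmation of successful bile duct cannulation, biliary sphincterotomy is performed". In section 2.7, the work before puncture includes scope insertion and this check: "Biliary accessibility is then confirmed via EUS from the duodenal bulb, with Doppler imaging used to rule out any intervening vessels". Bile aspiration, contrast, guidewire, any tract dilation and stent placement come after puncture.

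**Analysis.** For technical success, clinical success, success without tract dilation, procedure-related AEs, re-intervention success and post-drainage chemotherapy, section 3.2 says that percentages and "99% confidence intervals will be calculated for each group". Procedure time gets a mean and a 99% interval per group. The same paragraph names a two-sample log-rank test for patency and for overall survival.

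**Stated use.** The Discussion says: "This clinical trial will also compare the rates of technical success", and goes on to list the other shared rates, procedure time and overall survival. The Conclusions make possible replacement of ERCP conditional on superiority "in terms of stent patency and safety".

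**The concern.** These are two separate points. The procedure-time definition has no bearing on the rates.

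First, a between-arm difference in duration means something only if the clock measures the same span of work in both arms. Here one clock starts at puncture and the other at a step that the article elsewhere treats as completed access. If difficult cannulation is a main source of long ERCP procedures, the definition removes it from the ERCP time. Four centres could also read the ERCP start differently. A time stamp that was not recorded cannot be recovered at analysis.

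Second, the rates and procedure time are meant to be compared, and safety is part of the condition for the conclusion. The stated analysis stops at one interval per arm. A reader given two intervals side by side is likely to look at whether they overlap, and that is a much stricter criterion than the trial's own level of 0.01.

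**Working it through.** The article states no figure for the secondary endpoints, so there is none to reproduce. The procedure-time point is settled by reading the sections together, and the second point by a short calculation.

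**Step 1. The two clocks.**

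| | EUS-CDS | ERCP, start = success | ERCP, start = first attempt |
|---|---|---|---|
| Scope insertion | out | out | out |
| Finding the access site | out (scanning, Doppler) | out | out |
| Gaining access to the duct | in, from puncture | out | in |
| Work after access, to stent placement | in | in | in |

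The wording in 2.8 points to the middle column. There the ERCP time omits the effort to gain access, while the EUS-CDS time counts everything from the puncture on. Under the last column the two clocks are roughly parallel. EUS scanning is outside the clock on either reading. The article gives no scanning, cannulation or procedure times, so no net bias can be calculated. In addition, a procedure that never reaches stent placement has no time under the stated definition.

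**Step 2. What overlap of two intervals would mean.** Inputs: 99% intervals (3.2), two-sided level 0.01 (3.1), normal approximation.

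- Two intervals with standard errors s1 and s2 do not overlap when |difference| > z(s1 + s2), with z = 2.576.
- The standard error of the difference is √(s1² + s2²).
- With s1 = s2, the critical value is 2 × 2.576/√2 = 3.643, so the two-sided level is 0.00027.
- With s2 = 2 × s1, it is 2.576 × 3/√5 = 3.456, and the level is 0.00055.

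Equal standard errors are the extreme case. As they become more unequal, the level rises towards 0.01.

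**Step 3. The same in percentage points.** Assumption: 47 patients per arm, from the target of 95 and 1:1 allocation. Per-arm half-width h = 2.576 × √(p(1−p)/47). Non-overlap needs an observed difference above 2h. The half-width of the 99% interval for the difference is √2 × h.

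| Rate near | h | Needed for non-overlap | Half-width for the difference |
|---|---|---|---|
| 5% (or 95%) | 8.2 | 16.4 | 11.6 |
| 20% | 15.0 | 30.1 | 21.3 |

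**Step 4. Illustration with AE rates.** This is an exact enumeration of two binomials with 47 per arm. It compares non-overlap of Wilson 99% intervals with a pooled score test at 0.01. The 5% is the rate quoted in the Introduction for this stent. The article gives no AE rate for ERCP, so 20% and 30% are assumptions.

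| Assumed AE rates | Non-overlap | Direct test at 0.01 |
|---|---|---|
| 5% vs 20% | 4% | 34% |
| 5% vs 30% | 32% | 78% |

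**The case against.** Much of the case on the other side is sound.

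- A reader might infer that the promised comparisons cannot be made validly. For the rates that is wrong: allocation is randomised, counts will be known per arm, and a difference with its interval follows from them. What is lacking is a commitment to report it.
- A reader might infer that the trial will judge safety by interval overlap. Section 3.2 contains no such rule, so steps 2 to 4 measure what a likely misreading would cost, not a planned test.
- A reader might infer that procedure time is known to be biased in favour of ERCP. That depends on reading cannulation as success. Section 2.8 makes this plausible but section 2.10 does not say so. Puncture and cannulation are both duct-access steps, and site-finding before puncture is excluded too.
- A reader might infer that the conclusions already rest on superior safety. The sentence is conditional, and the hypothesis in 2.2 concerns patency alone.
- Estimation without tests is defensible for secondary endpoints in a trial sized for patency. Contrasts and the handling of failed procedures are often left to an analysis plan, which is not shown here.

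The last objection carries less weight than it first appears to. Section 3.2 is not silent: it specifies per-group intervals for these endpoints while naming a between-group test for overall survival, also secondary. That sits badly with the Discussion's promise. The start of the ERCP clock is an endpoint definition, and an analysis plan cannot repair it once the times have been recorded.

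**Conclusion.** Both points hold as minor ones on secondary endpoints. They leave the primary endpoint, the sample size and the main test untouched.

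**Procedure time.** The start steps differ and the ERCP start is ambiguous. If cannulation means success, as 2.8 suggests, the contrast favours ERCP on that component. The size, and the net direction once excluded EUS scanning is considered, cannot be determined from the article.

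**Comparison.** The analysis stated in 3.2 does not provide the comparison announced in the Discussion, although the data allow it. Used as an informal test, non-overlap would operate at about 0.0003 with equal standard errors. With 47 per arm it could miss differences that a direct test at 0.01 would often find. The AE rates behind that illustration are assumed.

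**What to change.** 1. In 2.10, use one start and end rule in both arms, for example scope insertion to stent deployment or to abandonment of the assigned procedure. Access-to-stent time can stay as a descriptive extra, with the ERCP start stated as first attempt or success. Cost: one more time stamp per procedure, and an endpoint that differs slightly from the present one.
2. In 3.2, add the between-arm risk difference with a 99% score-type confidence interval for each rate that both arms share, and the between-arm difference in procedure time with its 99% interval. Success without tract dilation applies to EUS-CDS only and stays per group. Cost: a few lines of text and no extra data beyond the time stamp. The intervals will be wide (step 3), which the report should say.

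The time stamp is the more urgent item, because it cannot be added after the procedures are done.
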